#### Secondary analysis

Differences in the levels of the proinflammatory cytokines TNF-alpha and IL-6 and differences in the PSS, PCS, and BDI-II scores will be compared between the intervention and wait-list control groups by a linear mixed-effects model. The baseline values of the scale and intervention group will serve as fixed factors, and the intercept will serve as a random factor. Moreover, the effects of demographics on the outcomes will be explored by considering them as fixed factors in the linear mixed-effects model. Finally, changes from baseline will be assessed by a linear mixed-effects model using linear contrasts.

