### Sample size

Sample size calculation will be based on a primary comparison of telomerase activity levels between the intervention and control groups. Based on a previous study that examined the effect of qigong on telomerase activity [27], the standard deviation will be set at 0.2. As in the study by Ho et al. we anticipate approximately 0.05 to 0.10 units of improvement in telomerase activity secondary to qigong. Thus, 113 subjects per group are required to detect a difference of at least 0.075 units between the two groups with 80% power and a ≤5% chance of a false-positive error. Allowing for a small rate of attrition, 240 women will be recruited and randomly assigned to either the intervention group (treatment condition, n = 120) or the wait-list control group (control condition, n = 120).

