### Procedures

Upon entry into the study (T0, baseline), women in both groups will be asked to complete the Chinese version of the Revised Conflict Tactics Scales (CTS2), Perceived Stress Scale (PSS), Perceived Coping Scale (PCS), and Beck Depression Inventory version II (BDI-II) as well as a demographic questionnaire. Blood samples will be collected from each of the participants by a research nurse trained for this purpose. The intervention group will then receive the qigong intervention. To monitor the self-practice of qigong by participants in the intervention group, we will adopt the recording and monitoring process that was successfully used in the earlier qigong intervention study conducted by our team members [27]. Specifically, each participant will enter on a record card the details of when she practices qigong, for how long, and how many times each day, together with the type and duration of other exercises undertaken in the same day. The participant will be required to submit the record card to our researcher to check the self-practice compliance at the weekly group follow-up sessions. The weekly monitoring will allow the researchers to undertake timely measures to address any early signs of noncompliance. Participants in the wait-list control group will be advised to avoid joining any outside qigong training classes because qigong exercise training will be provided to them after the final outcome measurement. Additionally, to reduce the risk of attrition, the control group will receive monthly health education sessions unrelated to qigong, commencing at the point at which the intervention group starts the weekly group follow-up.

When the intervention group begins the post-training and postintervention periods (T1 and T2, respectively), participants in both groups will complete the CTS2, PSS, PCS, and BDI-II. Blood specimens will be collected from the participants in both groups at T2. When the intervention group has completed the qigong intervention, participants in the wait-list control group will receive the qigong exercise training.

The immediate treatment received by the intervention group, the wait-list control condition received by the control group, and the data collection points is shown in Figure 1.

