### Measurements

#### Instruments

The following study instruments with the exception of the C-AAS and demographic questionnaire will be administered at three time points: (a) preintervention (T0, baseline); i.e., upon entry into the study, after randomization but before intervention; (b) post-training (T1, 6 weeks later); i.e., upon completion of the 6-week group learning and practice session; and (c) postintervention (T2, 5.5 months later); i.e., upon completion of the entire qigong intervention program. The C-AAS and demographic questionnaire will only be administered at baseline.The five-item *C-AAS*, which has demonstrated satisfactory psychometric properties [42], will be used to screen potential participants for IPV. If a woman answers “yes” to being emotionally, physically, or sexually abused within the past three years and if the perpetrator is her former or current intimate partner, she is considered to be positive for IPV.The *CTS2*, which has been validated with satisfactory validity and reliability [43], will be used to measure the type and frequency of behaviors used by the perpetrator during partner conflict. This 27-item instrument contains 8 measures of psychological aggression, 12 measures of physical assault, and 7 measures of sexual coercion. How often each behavior occurred within the preceding year is indicated by 0 = not within the past year, 1 = once, 2 = twice, 3 = 3 to 5 times, 4 = 6 to 10 times, 5 = 11 to 20 times, and 6 = 21 or more times.The 10-item *PSS*, the most widely used psychological instrument for measuring the perception of stress [44], will be used to assess the degree to which situations in life have been perceived by the participant as stressful during the past month. The PSS contains six negative and four positive items, and the overall score is obtained by reversing the responses to the four positive items (i.e., 0 [never] = 4, 1 [almost never] = 3, 2 [sometimes] = 2, 3 [fairly often] = 1, and 4 [very often] = 0) and then summing the response scores across all scale items. The PSS score may range from 0 to 40.The *PCS* [45] will be used to assess the types and perceived effectiveness of each of the 13 specific strategies used by the participant in dealing with violence perpetrated by her intimate partner. The strategies may be classified as active or passive; e.g., seeking assistance from family or friends, confronting the partner, redefining the meaning of the situation, or using alcohol or drugs. Scoring is based on a four-point Likert scale: 1 (not at all helpful), 2 (not so helpful), 3 (somewhat helpful), and 4 (very helpful).The Chinese version of the *BDI-II* will be used to assess depressive symptoms experienced within the previous 2 weeks. This 21-item instrument has established construct validity and reliability for Chinese populations [46]. The score may range from 0 to 63, with 0 through 13 indicating minimal depressive symptoms, 14 through 19 indicating mild depressive symptoms, 20 through 28 indicating moderate depressive symptoms, and 29 through 63 indicating severe depressive symptoms.A *demographic questionnaire* will be used to elicit the following information: age of the participant and her partner, education level, place of birth, number of years living in Hong Kong, marital status, duration of the abusive relationship, number of children, employment status of the participant and her partner, financial hardship, receipt of comprehensive social security assistance, need for financial support, and history of chronic illness.

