### Data analysis

The primary outcome in this study will be the telomerase level as measured by telomerase activity at postintervention (T2). The secondary outcomes will be the proinflammatory cytokines TNF-alpha and IL-6, perceived stress as measured by the PSS, perceived coping as measured by the PCS, and depressive symptoms as measured by the BDI-II at postintervention (T2).

Data analysis will be performed using Statistical Analysis System software. Each estimated effect will be accompanied by a 95% confidence interval where appropriate. Unless otherwise specified, a 5% level of significance will be used. All statistical methods will be checked for validity before interpretations are made.

The baseline (T0) characteristics between the intervention and wait-list control groups will be assessed by a chi-squared test and Mann–Whitney U test for categorical and continuous data, respectively.

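### For PSS, PCS and BDI-II the secondary mixed model lists no visit terms, so its group effect averages T1 and T2 instead of estimating the stated T2 outcome

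*Protocol article*

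**What the plan says.** All references are to the protocol article.

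- **Outcome.** The Data analysis section places the five secondary outcomes (TNF-alpha, IL-6, PSS, PCS, BDI-II) at T2. Its list ends with "depressive symptoms as measured by the BDI-II at postintervention (T2"). The hypotheses under Aims likewise refer to the end of the programme.
- **Visits, scales.** The Instruments section says that the questionnaires "will be administered at three time points": T0, T1 at 6 weeks and T2 at 5.5 months. Each scale therefore has two values after baseline.
- **Visits, cytokines.** Blood is taken at baseline, and then, under Procedures, "Blood specimens will be collected from the participants in both groups at T2". TNF-alpha and IL-6 therefore have one value after baseline.
- **Model.** The Secondary analysis section uses a linear mixed-effects model for all five outcomes and gives its terms: "The baseline values of the scale and intervention group will serve as fixed factors, and the intercept will serve as a random factor". Demographics may be added as exploratory fixed factors. Visit and group-by-visit are not named.
- **Change.** The same section ends by saying that "changes from baseline will be assessed by a linear mixed-effects model using linear contrasts". It does not give the terms of that model or say whether it is the one just described.

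**The concern.** The section states a set of model terms, and for the three scales those terms do not match the stated outcome. With baseline as a covariate, T1 and T2 are the repeated responses. One group coefficient then has to describe both visits.

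The article gives reasons not to take equal effects at the two visits for granted. The Intervention section totals 103 hours of qigong. By T1 a woman has had 24 group hours and at most 6 × 7 × 0.5 = 21 hours of daily self-practice, so between 24/103 = 23% and 45/103 = 44% of the total. Under Procedures, the control group's monthly health education begins only when the weekly follow-up begins, which is after T1. An average over the two visits therefore mixes different amounts of exposure and two control conditions.

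If the effect builds over 5.5 months, the averaged coefficient understates the effect at T2. If it fades, the coefficient overstates it. PSS is among the affected scales, and psychological stress is in the trial's title. Leaving the matter open also leaves a later choice between an averaged result and a T2 result.

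**Working it through.** **The plan's own figure.** The only related figure is the sample size for telomerase. The Sample size section says "the standard deviation will be set at 0.2" and "113 subjects per group are required to detect a difference of at least 0.075 units between the two groups with 80% power", with "a ≤5% chance of a false-positive error". The two-sided normal formula gives n = 2[(1.960 + 0.842) × 0.2/0.075]² = 111.6, so 112 per group. The t-test version gives 112.6, so 113. The stated figure reproduces and does not depend on the secondary model, which has no stated figure of its own.

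**Scales, algebra.** Let Δ1 and Δ2 be the true group effects at T1 and T2. The listed model is

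Y(i,t) = β0 + β1·Y(i,0) + β2·Group(i) + b(i) + e(i,t), for t = T1, T2.

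Baseline and group do not vary within a woman. With both visits observed, the estimate of β2 is that of a regression on each woman's mean of T1 and T2. Its expectation is (Δ1 + Δ2)/2. Writing Δ1 = f·Δ2, the ratio to the T2 effect is (1 + f)/2: 0.50 for f = 0, 0.75 for f = 0.5, 1.00 for f = 1 and 1.25 for f = 1.5.

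**Scales, simulation.** The following inputs are assumed and are not in the documents: SD 6, within-woman correlation 0.5, Δ2 = −3, 120 women per arm, complete data, 60 replicates per scenario.

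| f | Theory, −3(1 + f)/2 | Listed model | With visit and group-by-visit, T2 contrast |
|---|---|---|---|
| 0 | −1.50 | −1.41 | −2.88 |
| 0.5 | −2.25 | −2.24 | −3.01 |
| 1 | −3.00 | −2.97 | −2.90 |
| 1.5 | −3.75 | −3.74 | −2.99 |

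The standard error of one baseline-adjusted T2 estimate is 6√(1 − 0.5²) × √(2/120) = 0.67, so a mean of 60 carries simulation error of about 0.67/√60 = 0.09. The last column is consistent with −3 throughout.

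**Scales, change from baseline.** Without a visit term, the fitted group mean is the same at T1 and T2. The fitted change from T0 to T1 then equals that from T0 to T2, so visit-specific changes cannot be obtained.

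The baseline covariate is not the obstacle. Subtracting Y(i,0) from both sides of a T2 regression changes β1 to β1 − 1 and leaves the group coefficient as it was. In the simulated T2-only fits, the group coefficient for level and for change differed by about 3 × 10⁻¹⁴. In one data set, the adjusted within-group changes were 0.515 (control) and −2.322 (intervention) from either model.

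**Cytokines.** With one follow-up value, the model is Y(i,2) = β0 + β1·Y(i,0) + β2·Group(i) + b(i) + e(i). Here β2 is the T2 difference. Only the sum of the variances of b and e can be estimated, so the random intercept is redundant.

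**The case against.** The best reply is that the Secondary analysis section does not name the response visits, while the Data analysis section fixes the outcomes at T2. Read together, the model could be meant for T2 scores only, and β2 would then be the right quantity. This stands as a possible reading, and it means that the averaging is an inference from the random intercept and the visit schedule. It does not rescue the text. With one value per woman, the random intercept cannot be separated from residual error, so the stated model needs correcting on either reading.

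A second reply is that an article condenses its protocol, and visit coding is commonly left to an analysis plan that is not shown. That would answer a charge of missing detail. Here, however, the terms are listed, and as listed they do not fit the stated outcome for three scales.

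Some stronger readings are tempting, but the documents do not support them:

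- *That no secondary outcome is estimated at T2.* This is untrue for TNF-alpha and IL-6, as shown above.
- *That baseline adjustment rules out change-from-baseline estimates.* It does not. The sentence on change also speaks of a mixed model in general and may mean a separate one with a visit factor.
- *That T0 is also a response, which would dilute the effect further.* With f = 0.5 this would give −1.5 for a true −3 (simulated −1.53), but the article never says that baseline enters as both covariate and response.
- *That the missing visit term alone lets T1 scores stand in for T2 in women lost before T2.* The Primary analysis section replaces missing values by the last observed ones. If that rule extends to the scales, the substitution happens even with visit terms in the model.

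**Conclusion.** The point holds for PSS, PCS and BDI-II, three of the five secondary outcomes. As listed, and fitted to T1 and T2, the model estimates the average of two visit effects, where the Data analysis section asks for the effect at T2. It also cannot give visit-specific changes for these scales.

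The reported effect would be 50%, 75%, 100% or 125% of the T2 effect for a T1 effect of 0, 0.5, 1 or 1.5 times the T2 effect. These percentages assume both follow-up scores in the response, equal weights (complete follow-up), and a T1 effect that the documents do not give. If the two effects are equal, there is no discrepancy.

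For TNF-alpha and IL-6 the fault is only a redundant random intercept. The telomerase analysis is tied to T2 and is not touched, nor is the sample size. The text should be fixed before analysis, but the trial's main conclusion does not depend on it.

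**What to change.** In the Secondary analysis section, or in the analysis plan that governs it:

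1. For PSS, PCS and BDI-II, keep baseline and the random intercept, and add visit (categorical) and group-by-visit as fixed effects, with T1 and T2 as responses.
2. Name the group contrast at T2 as the secondary test and describe the T1 contrast as supportive.
3. State the model behind the change-from-baseline contrasts, and take those for the scales from a model that includes visit.
4. For TNF-alpha and IL-6, use baseline-adjusted regression at T2, as already planned for telomerase.

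The cost is a change of wording. No new data or visits are needed, and the sample size stays as it is.

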### Ethical issues

This protocol was approved by the Institutional Review Board of the University of Hong Kong/Hospital Authority Hong Kong West Cluster (HKU/HA HKW IRB: UW 12–555) on 9 January 2013.The study will be conducted according to the Declaration of Helsinki. Participation in the study is voluntary. An information sheet will be provided and a written consent is required from all participants.

In our extensive experience of working with abused women, we have found that they generally appreciate explaining their experience of abuse to professionals who have been trained to validate this experience. In this study, they will also be offered an opportunity for follow-up with a social worker if necessary. If they choose to withdraw from the study, they may do so with no questions asked.

## Discussion

This study protocol provides a detailed account of the implementation and evaluation of a qigong intervention for abused Chinese women. This will be the first randomized controlled trial to evaluate the effect of qigong on the telomerase activity and psychological stress levels of Chinese women who experience IPV.

The findings of this study will not only provide new knowledge supporting the design of other interventions to buffer the effects of IPV-related psychological stress on health, but they may also support the idea that health behaviors, such as qigong, can counter accelerated cellular aging and thus motivate abused women to change their lifestyles. These trial findings may also motivate professionals to provide timely interventions that interrupt declines in patient health and reduce suffering among abused women with the potential to lower IPV-related health costs.

This study will be conducted in Hong Kong in a group of community-dwelling Chinese women whose experience of IPV may or may not have been previously brought to the attention of social services or health professionals. This qigong intervention adds to the list of psychosocial interventions already available to abused Chinese women, including (i) a 30-minute session of empowerment intervention provided once by an antenatal clinic [53], (ii) a 3-week intervention providing empowerment training, legal advocacy, parenting training, and a Chinese medicine dietary regimen in a shelter setting [38],and (iii) a 12-week empowerment intervention with social support in a community setting [40]. This qigong intervention differs from the above-listed interventions by engaging women in health behaviors that empower them to better manage IPV-related psychological stress and hopefully attenuate the associated adverse health effects. As such, the results of this qigong intervention may expand the scope of interventions for abused Chinese women.
